#### Data management

Anonymized participant data will be entered into the electronic research database (internet-based Clinical Research and Trial management system, iCReaT). The iCReaT system was created by the government and designed so that investigators and researchers can securely and directly input patient research data. This database is equipped with several security devices to protect data and prevent unauthorized access and information disclosure using a web-based encryption system. All data is assigned to each patient’s study number and processed anonymously. This study number is provided to the researchers and investigators only. The anonymized outcome data is only available and accessible to the leading researchers, investigators, and statistical analysts.

Designated monitoring researchers, delegated by the primary monitoring researcher, will carry out checks to determine if the clinical trial is being conducted per the Korea Good Clinical Practice and related regulations and according to the clinical trial protocol. Monitoring will be conducted in parallel with on-site (i.e., institution visits) and in-house monitoring (i.e., through the electronic data capture system). On-site monitoring will be conducted ten times in total, including the site initiation visit and the site close-out visit. In this study, the dataset from the electronic case report form (e-CRF) system will be used, and the clinical research associate from the contract research organization will monitor the completeness and accuracy of the data collected by the researchers. Data with problems or questions will be sent to the researcher through the e-CRF system query function to check and correct the data. The modified database will be saved, and all changes to the database will be recorded. All research documents will be coded and stored separately and managed so that personal identification through the data is impossible.

#### Safety reporting

Regarding the biportal endoscopic discectomy and microscopic discectomy to be performed in this trial, there are no additional complications due to participation of this trial. Complications of general spinal surgery, such as bleeding, infection, dural tear, nerve root damage, bowel and bladder incontinence, pneumonia, deep vein thrombosis, and requirement for revision surgery should be fully explained before the start of the trial.

If unexpected adverse events occur during the course of this trial, the researcher should immediately report it to the institutional review board of the relevant hospital, the principal investigator, and the sponsor. Also, if the participant needs treatment, first aid is implemented as soon as possible. Adverse reactions that occurred during the trial will be followed up until symptoms resolved or stabilized.

Any harm from the intervention that occurred to the participants during this trial will be divided into adverse events (AEs), serious adverse events (SAEs), and suspected unexpected serious adverse reactions (SUSARs). The chart is drawn up in the order of symptom occurrence according to the severity, and participants check it when they visit the outpatient clinic. Adverse reactions should be described in detail in the special form of the case report form regarding symptoms, duration, severity, causal relationship with intervention, additional treatment, results of adverse reactions, and severity.

#### Sample size

This trial will recruit 100 participants (50 participants per group) to confirm the primary outcome equivalence between biportal endoscopic and microscopic discectomy. According to a previous report [21], the minimal clinically important ODI difference was 12.8, and in the previous study [22], the standard deviation of the ODI value 1 year after endoscopic discectomy was 17.1. Assuming that the equivalence limit is 12.8, alpha = 0.05, power = 0.90, two-sided 95% CI, and the follow-up loss = 20%, 50 participants are needed for each group. Power Analysis and Sample Size software version 15 (NCSS, Kaysville, UT, USA) was used for calculating the sample size.

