#### Statistical analysis

All statistical analyses will be conducted using Stata/MP 15.1 (StataCorp LLC, College Station, TX). A two-sided *P*-value < 0.05 will be considered statistically significant. The Shapiro-Wilk test will be used to evaluate the distribution of the collected data. Normally distributed continuous variables will be presented as the mean and standard deviation (SD), whereas non-normally distributed variables will be presented as the median and interquartile range. Categorical variables will be presented as numbers and percentages (%).

Both modified intention-to-treat (mITT) and per-protocol analyses will be performed. The mITT strategy will be the main analysis and indicates that participants are analyzed on whether they underwent a randomly assigned surgery (to avoid the effects of crossover and dropout, which may break the random assignment to the treatment groups). Excluded participants before and after surgery will be excluded from the analysis, and participants exceeding the calculated sample size will not be recruited.

The surgical intervention effect 12 months after surgery will be assessed by the ODI scores and a two-sided 95% confidence interval (CI) as the primary outcome and then compared between the groups. Biportal endoscopic discectomy will be considered equivalent to microscopic discectomy if the upper and lower limit of 95% CI of the ODI score at 12 months is limited to within the pre-defined equivalence limit of 12.8 points. To analyze the serial effect on secondary clinical outcomes (i.e., VAS pain scores for the back and lower extremities and the ODI, EQ-5D, and POSAS score), a linear repeated-measures mixed model will be used. Time will be analyzed as a categorical variable (2 weeks and 3, 6, and 12 months) and include the intervention-time interaction to analyze the effects of surgery during the follow-up periods. Inter-group differences during the 12-months will also be analyzed using a linear repeated-measures mixed model, controlling for baseline and follow-up time points as categorical variables. Other clinical, radiographic outcomes and adverse effects between two groups will be analyzed using Student’s *t*-test for continuous variables and the chi-square test for categorical variables.

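### Under the plan's own 95% CI rule, 50 per group with the planned 20% loss gives about 82% power for equivalence, not the stated 90%

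*Protocol article*

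**What the plan says.** The Sample size section of the protocol article takes 12.8 ODI points as the equivalence limit and reports that "the standard deviation of the ODI value 1 year after endoscopic discectomy was 17.1". It then gives the remaining inputs and the result: "alpha = 0.05, power = 0.90, two-sided 95% CI, and the follow-up loss = 20%, 50 participants are needed for each group". The total is 100 participants, allocated 1:1.

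The Statistical analysis section sets the success criterion for the primary outcome. The two procedures count as equivalent on this condition: "if the upper and lower limit of 95% CI of the ODI score at 12 months is limited to within the pre-defined equivalence limit". That limit is the same 12.8 points used for the sample size. The same section says of losses: "Excluded participants before and after surgery will be excluded from the analysis".

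A 90% CI is mentioned nowhere. The article does not say whether alpha = 0.05 applies to each one-sided test or to both together, and it gives no assumed true difference.

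**The concern.** Equivalence of two means is tested with two one-sided tests. Requiring a two-sided 95% CI to lie inside the margin is the same as running each test at 2.5%. Running each at 5% corresponds to a 90% CI. Sample-size software for equivalence commonly takes alpha per one-sided test, so entering 0.05 there sizes the trial for a 90% CI even if the text says 95%. The question is whether 50 per group provides 90% power under the rule the trial will actually apply.

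Equivalence at 12 months is the trial's primary claim, and the Abstract and Discussion rely on an adequate sample size to promise clear conclusions. If power is lower than stated, an inconclusive result is more likely than readers have been told. There is also room for dispute afterwards: if the 90% CI fitted inside the margin and the 95% CI did not, the sample-size basis could be cited in favour of the looser reading.

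**Working it through.** **Inputs**

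- Margin M = 12.8 and SD = 17.1, taken as common to both arms (Sample size).
- Stated power 0.90, alpha 0.05, loss 20%, 50 per group (Sample size).
- Decision rule: both limits of the two-sided 95% CI within 12.8 (Statistical analysis).
- Analysed number per group: 50 × 0.8 = 40.
- Assumption: true difference 0. The article does not state it. It is the most favourable value and fits the hypothesis in the Background that results will be similar.

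**Formulas**

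Normal approximation with true difference 0 and 90% power, beta split over the two sides:

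n per group = 2 × (z₁₋ₐ + z₀.₉₅)² × (SD/M)², where a is the error per side.

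Standard error of the difference: SE = SD × √(2/n).

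Power: approximately 2Φ(M/SE − z₁₋ₐ) − 1. The exact version uses the t quantile with 2n − 2 degrees of freedom and integrates over the sampling distribution of the pooled SD.

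**Step 1. Reproduce the plan's figure**

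With 5% per side (90% CI): n = 2 × (1.645 + 1.645)² × (17.1/12.8)² = 38.6. Exact power is 89.7% at 39 per group and 90.6% at 40, so 40 is the smallest number that reaches 90%. Inflating for loss, 40/0.8 = 50, which is the stated figure exactly.

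**Step 2. Apply the plan's decision rule**

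With 2.5% per side (95% CI): n = 2 × (1.960 + 1.645)² × (17.1/12.8)² = 46.4. Exact power is 89.7% at 47 and 90.5% at 48, so 48 analysed are needed, and 48/0.8 = 60 per group (120 in total).

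At the planned 40 analysed, SE = 17.1 × √(2/40) = 3.82 and M/SE = 3.35. Normal approximation: 2Φ(3.35 − 1.96) − 1 = 83.5%. Exact: 82.2%.

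| Analysed per group | Loss from 50 | Exact power, 90% CI | Exact power, 95% CI |
|---|---|---|---|
| 40 | 20% | 90.6% | 82.2% |
| 45 | 10% | 94.0% | 87.9% |
| 48 | 4% | 95.4% | 90.5% |
| 50 | 0% | 96.2% | 91.9% |

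**Step 3. Try other routes to 50**

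- A one-sided 2.5% formula without splitting beta (a non-inferiority calculation), or a two-sided 5% superiority formula, gives 38 analysed and 48 per group.
- A one-sided 5% non-inferiority formula gives 31 analysed and 39 per group.

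Neither gives 50, and neither is an equivalence calculation. With 38 analysed, equivalence power under the 95% CI rule is 79.2%.

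**Step 4. Sensitivity to the true difference** (illustrative values, not from the article)

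At 40 analysed under the 95% CI rule, power is 80.7%, 76.5% and 69.9% for true differences of 1, 2 and 3 points.

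**The case against.** The strongest points on the other side are these.

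- **The two sections do not disagree in their words.** Both specify a two-sided 95% CI. This is correct: the fault is that 50 per group does not follow from the stated inputs. That the calculation was run at 5% per side is inferred from the exact match and is not something the article says. The shortfall does not depend on that inference, because 40 analysed per group gives 82% under the 95% CI rule whatever formula was used.
- **The error is on the safe side.** The rule is the stricter one, so a positive equivalence finding keeps its validity. This stands. What suffers is the stated power, not the false-positive risk.
- **82% applies only if the full 20% is lost.** Also correct; with no loss, power is 91.9%. But 20% is the plan's own assumption, and the stated 90% is given on that basis.
- **Zero is the usual default for the true difference, and a condensed article may omit it.** Accepted. Its absence is a point of wording, and the results for 1 to 3 points are illustrations only.
- **Applying the CI to the ODI score is loose wording that the context resolves.** Accepted. The primary outcome is defined as a comparison between the groups, and a margin of 12.8 makes sense only for a difference. This is editorial and adds no weight to the arithmetic.

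**Conclusion.** The concern holds. With margin 12.8, SD 17.1 in both arms, true difference zero and the planned 20% loss, 50 per group gives 82.2% power under the stated 95% CI rule, about 8 percentage points below the claimed 90%. The chance of failing to show equivalence between identical procedures is 100 − 82.2 = 17.8%, against the 10% implied. Any true difference other than zero lowers power further. The stated 90% is reached only if at least 48 of 50 per group are analysed, or if 60 per group are randomised with 20% loss. The type I error of the equivalence claim is unaffected. The most likely cause is that alpha was entered as 5% per one-sided test, but the conclusion does not rest on this.

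**What to change.** Keep the 95% CI rule and correct the power statement. Suggested wording for the Sample size section: *With 40 evaluable participants per group (50 randomised, 20% loss), an SD of 17.1 and a true difference of zero, power to show equivalence using the two-sided 95% CI is about 82%.*

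In the Statistical analysis section, write the criterion as: *the two-sided 95% CI of the between-group difference in mean 12-month ODI lies entirely within −12.8 to +12.8.*

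This costs two sentences and no extra patients, and leaves the analysis unchanged. The price is a less favourable stated power.

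If the sponsor wants to retain 90% power with 20% loss, the consistent alternative is 60 per group, 20 more participants in total. Moving to a 90% CI would match the existing number, but it would double the per-side error of a published rule after recruitment began in July 2021. It is a trade-off to be justified, not a correction, and is not recommended here.

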#### Ethics and dissemination

The design and protocol of this multicenter, assessor-blind, prospective, RCT have been approved by the institutional review board of six hospitals (Seoul National University Bundang Hospital, B-2102/666-007; Hallym University Kangnam Sacred Heart Hospital, HKS202102023-HE002; Chung-Ang University Hospital, 2120-006-453; Korea University Anam Hospital, 2021AN0128; Wiltse Memorial Hospital, 2021-W01; Seoul Bumin Hospital, etc._21_003). All modifications that may affect the research data will be approved by the research ethics committee before implementation.

The study results will be submitted for peer-review publications. Additionally, electronic data will be anonymized and uploaded to an electronic database server (iCReaT) that supports limited access. Electronic data will not be made publicly available, and access to the data set will only be provided by the data management committee of the government’s research consortium.

## Discussion

Discectomy has developed over time. In 1977, Caspar et al. introduced microscopic discectomy, a less invasive method compared to conventional technique [23]. After the introduction of percutaneous posterolateral discectomy by Parvis Kambin in 1987 to reduce paraspinal muscle damage, percutaneous endoscopic lumbar discectomy (PELD) has been widely used, and this can be considered the beginning of endoscopic discectomy [24]. However, PELD has limitations in movement by docking an endoscope on the lesion, and it is not effective in nerve compression or stenosis caused by degenerative osteophytes. In 2013, Soliman first introduced the concept of biportal endoscopic surgery [25]. During this surgery, one can freely manipulate surgical instruments through two portals, secure a wider field of view, and remove the osteophyte by using a burr or osteotome more easily.

There have been some previous studies on the efficacy of biportal endoscopic discectomy [7, 14, 15]. In a multicenter, retrospective analysis of 141 patients with single-level lumbar disc herniation, biportal endoscopic discectomy yielded similar clinical outcomes, including pain control, functional disability, and patient satisfaction, compared to open microscopic discectomy and showed minimal estimated blood loss, shorter hospital stay, and less early postoperative back pain [8]. In addition, there are some studies that have reported that it can be applied even in complicated cases. Kang et al. reported that biportal endoscopic discectomy showed satisfactory clinical outcomes even in cases of high-grade migrated lumbar disc herniation [26]. Moreover, Kang et al. compared biportal endoscopy and open microscopy with revisional discectomy and reported that both techniques showed similar clinical outcomes at 1 year after surgery. The biportal endoscopic group showed faster pain relief, earlier functional recovery, and better patient satisfaction [13]. Thus, biportal endoscopic discectomy may be a feasible option.

However, studies on biportal endoscopic discectomy have limitations as retrospective studies, and an RCT has not yet been performed. This trial will be the first prospective, multicenter, RCT to analyze the efficacy and safety of biportal endoscopic discectomy in lumbar herniated disc. This trial is designed for evaluating the equivalence of the results between biportal endoscopic and microscopic discectomy including adequate sample size, blinded analyses, and prospective registration to reduce bias. This trial will provide enough data on the effectiveness and safety of biportal endoscopic surgery and will be an important study that allows clear conclusions.

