## Background

Discectomy for herniated discs is the most common method for resolving a patient’s symptoms [1, 2]. Currently, microscopic discectomy, a minimally invasive surgery, is performed to address the problems of conventional open discectomy [3]. As a representative method, microscopic discectomy, which uses a tubular retractor and an endoscope, is the most commonly used minimally invasive surgery method [1]. Minimally invasive surgery has many advantages over conventional methods, and reports indicate that the clinical results do not differ from conventional methods [3, 4]. A full-endoscopic discectomy (uniportal) is a minimally invasive surgery with a single very small incision. According to a randomized controlled trial by Gibson JNA et al., full-endoscopic discectomy showed similar functional improvement compared to microscopic discectomy, and it showed reduced length of hospital stay and less leg pain at 2 years after surgery [5]. However, the procedure is difficult to learn, has a narrow field of view and a long operation time, and may cause problems, such as insufficient discectomy [6].

Recently, the biportal endoscopic spine surgery was developed [7–13]. This surgical technique uses two small skin incisions, called portals, to access the surgical site, minimizing the damage to normal structures. Consequently, there are fewer post-surgical complications, such as postoperative pain and muscle damage. Additionally, arthroscopic instruments for knee and shoulder joint surgery can be used, eliminating the need to purchase additional equipment. Spinal instruments familiar to the spine surgeon, such as Kerrison punches and pituitary rongeurs, can also be used.

There are several retrospective clinical reports of biportal endoscopic discectomy [7, 14, 15]. A previous study reported that the clinical feasibility and results of biportal endoscopic discectomy were similar to conventional discectomy. However, the evidence suggesting advantages to biportal endoscopic discectomy was weak owing to the small number of patients, and the study was retrospective. Therefore, a randomized controlled trial (RCT) is warranted. This multicenter, prospective RCT will compare the outcomes of biportal endoscopic versus microscopic discectomy. We hypothesize that the efficacy and safety of biportal endoscopic discectomy and microscopic discectomy in the lumbar spine will be similar.

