#### Secondary outcome

The secondary outcomes are the clinical outcomes, radiographic outcomes, and adverse events. Clinical outcomes include (1) low back pain and lower extremities radiating pain, measured based on the VAS pain score, which ranges from zero (i.e., “none”) to 10 (i.e., “severe pain”), (2) quality of life (QOL), measured by the EuroQol-5-dimension-5-level [EQ-5D] questionnaire, which contains five questions with five responses for each question, and the total score is converted into the final EQ-5D value, ranging from 0.000 to 1.000; higher scores indicate a better QOL [18], (3) surgery satisfaction, (4) walking time, (5) the postoperative return to daily life period, (6) postoperative surgical scarring, measured by the Patient and Observer Scar Assessment Scale [POSAS] patient scale 2.0, containing six parameters with 10-point scoring system; 6 represents normal skin, and 60 represents the worst scar imaginable, and (7) surgery-related variables, such as postoperative drainage (mL), operation time (minutes), admission duration (hours), postoperative creatine kinase, and implementation status of conversion to open surgery. The radiographic outcomes include (1) the degree of disc removal and facet joint injury, measured using postoperative MRI or CT and (2) other radiographic complications, measured using simple radiographs during the follow-up period. Safety will be assessed by evaluating all adverse and severe adverse events and surgery-related effects (reported to the appropriate institution, as needed). This will be reported by the participant to the surgeon or the assessor and recorded in the electronic database.

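### The chi-square test of difference planned for adverse effects at 50 per arm cannot support the hypothesis of similar safety or the claim of enough safety data for clear conclusions

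*Protocol article*

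**What the plan says.** The Background states one hypothesis with two halves: "We hypothesize that the efficacy and safety of biportal endoscopic discectomy and microscopic discectomy in the lumbar spine will be similar". The Discussion closes by saying that the trial "will provide enough data on the effectiveness and safety of biportal endoscopic surgery and will be an important study that allows clear conclusions", and the Discussion part of the Abstract makes the same claim.

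The methods treat the two halves differently:

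- **Efficacy.** Under Statistical analysis, equivalence is concluded if the 95% CI for the 12-month ODI "is limited to within the pre-defined equivalence limit of 12.8 points". Under Sample size, the trial recruits "100 participants (50 participants per group) to confirm the primary outcome equivalence".
- **Safety.** Under Secondary outcome: "The secondary outcomes are the clinical outcomes, radiographic outcomes, and adverse events". Under Statistical analysis: "Other clinical, radiographic outcomes and adverse effects between two groups will be analyzed", with Student's t-test for continuous variables and "the chi-square test for categorical variables". The general rule there is that a two-sided P-"value < 0.05 will be considered statistically significant".

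The article gives no margin, confidence-interval rule, expected event rate or power for any safety outcome.

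**The concern.** A chi-square test takes no difference as its null hypothesis. Rejecting the null is evidence of a difference, but failing to reject is not evidence of similarity, least of all when events are few. For safety, the hypothesis is one of similarity while the planned method can only detect dissimilarity. The ODI does not have this problem, because its CI is compared with a margin.

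The article describes this as the first prospective multicentre randomised trial of the technique, so its safety statement is likely to carry weight. If the adverse-event table shows P > 0.05 beside a hypothesis of similar safety and a promise of clear conclusions, a reader could take the two operations to be equally safe when the data still allow a materially higher complication rate in either arm.

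**Working it through.** **Inputs from the article.** 50 per group, 1:1; two-sided 0.05; chi-square test for categorical outcomes; 20% loss to follow-up assumed; ODI margin 12.8, SD 17.1, power 0.90.

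**Inputs that are assumptions.** The article lists possible complications under Safety reporting but gives no frequencies. I use control-arm rates of 2%, 5% and 10%, for one yes/no safety outcome per patient.

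**1. The stated sample size.** It concerns the ODI only. For two one-sided tests at 0.05 each with true difference zero, n = 2 × [SD × (z0.95 + z0.95) / margin]² = 2 × [17.1 × (1.645 + 1.645) / 12.8]² = 38.6, so 39 per arm. The t-based version gives 40, and 40 / 0.8 = 50, which is the stated figure. (Whether that calculation matches the two-sided 95% CI rule is a separate matter.) No safety quantity enters it.

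**2. Power of the planned safety test.** All pairs (x₁, x₂) with x₁, x₂ = 0 to n are enumerated. The binomial probabilities are summed over pairs where |z| > 1.96, with z = (x₁ − x₂)/n ÷ √[p̄(1 − p̄)·2/n] and p̄ = (x₁ + x₂)/2n. This is the uncorrected Pearson chi-square.

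| Assumed true rates | Exact power, 50 v 50 | Exact power, 40 v 40 |
|---|---|---|
| 2% v 4% (doubling) | 0.05 | 0.04 |
| 5% v 10% (doubling) | 0.14 | 0.15 |
| 10% v 20% (doubling) | 0.30 | 0.25 |
| 2% v 6% (tripling) | 0.14 | 0.11 |
| 5% v 15% (tripling) | 0.39 | 0.35 |
| 10% v 30% (tripling) | 0.73 | 0.63 |

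The 5% v 10% value at 50 per arm is 0.145 before rounding. The 40 v 40 column shows the planned 20% loss, because the plan drops participants excluded after surgery from the analysis. Power does not fall smoothly with n here because the counts are discrete. Over these base rates a true doubling is missed in about 70% to 95% of trials at 50 per arm.

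**3. What a non-significant result would leave open.**

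- *3/50 v 3/50.* The Wilson limits for 3/50 are 0.0206 and 0.1622. The Newcombe half-width is √[(0.06 − 0.0206)² + (0.1622 − 0.06)²] = 0.109, so the 95% CI of the risk difference is about ±11 percentage points.
- *3/50 v 9/50.* p̄ = 12/100 = 0.12, so z = 0.12 / √(0.12 × 0.88 × 2/50) = 1.846, chi-square = 3.41 and P = 0.065. A threefold observed difference is non-significant. The Newcombe 95% CI runs from about −1 to +25 points.
- *0/50.* The exact two-sided 95% upper limit is 1 − 0.025^(1/50) = 0.071, so a true rate of up to 7.1% is not excluded.

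**4. What a formal safety equivalence claim would need.** Per arm, n = 2p(1 − p)[(z0.975 + z0.90)/margin]² for 80% power with equal true rates. At p = 5% and an assumed margin of 10 points: 2 × 0.0475 × (3.2415/0.10)² = 99.8, so 100 per arm. With a 5-point margin, 400 per arm. At p = 10%, 190 and 757 per arm. Each of these exceeds 50.

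**The case against.** The strongest reply is that the article never takes the harmful step. A reader might infer that the plan will treat a non-significant chi-square result as proof of similar safety. No section says so: the only equivalence rule is the one for the ODI, and adverse effects get a comparison with no similarity decision attached. This stands, and the point is therefore that the result may be misread, not that the plan prescribes the misreading.

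Three further replies carry weight:

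- **Safety is secondary.** A secondary safety outcome without a margin or power of its own is ordinary in an equivalence trial. This stands, and the ODI conclusion is untouched.
- **The rates are assumed.** It would be tempting to say that a tripling of complications would generally be missed. That does not hold: 10% v 30% is detected with power 0.73, and 15% v 45% with 0.92. The doubling result is sturdier, but it too depends on the base rate (0.44 at 15% v 30%).
- **Interval methods and complication tables can be left to the SAP, and a hypothesis in the Background need not be confirmatory.** Both stand. It would be too much to demand that safety be struck from the hypothesis.

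These replies do not remove the mismatch. The article names a test, states a safety hypothesis that this test cannot address, and claims a capability that nothing in its design supplies. All three are stated in the text, so this is not a gap that a fuller document might fill.

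**Conclusion.** The concern holds in this limited form: the stated test cannot support similar safety, and the claim of enough safety data for clear conclusions goes beyond a design sized on the ODI alone. At 50 per arm, exact power for a doubling is about 5% to 30% over assumed base rates of 2% to 10%. For a tripling it is 14% to 73% over the same range. Equal counts of 3/50 leave about ±11 percentage points open.

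The power figures rest on the assumed rates, a single yes/no outcome and an uncorrected chi-square test. The mismatch between hypothesis and test does not depend on them. The point is worth correcting, but it does not threaten the primary analysis.

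**What to change.** 1. **Statistical analysis.** For adverse effects, replace the chi-square P-value as the basis of comparison with the risk difference and its 95% CI (Newcombe or exact). These intervals also suit small counts better: at a 5% rate only 0.05 × 50 = 2.5 events per arm are expected, too few for the chi-square approximation to be reliable.
2. **Same section.** State that the safety comparison is descriptive and that a non-significant difference will not be taken as similarity.
3. **Background.** The safety hypothesis may stay if it is labelled exploratory.
4. **Abstract and Discussion.** Limit the claims of enough data and clear conclusions to equivalence on the 12-month ODI.

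No extra participants, visits or data are needed. The cost is a small change to the analysis text and a more modest safety claim. A confirmatory safety claim would instead need a justified margin and, on the assumptions above, at least 100 per arm.
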